### Randomisation

Participants who meet the inclusion/exclusion criteria and want to participate in the study will be randomly assigned to either the treatment-as-usual group or the intervention group (treatment-as-usual plus a strength-based training programme.) We shall carry out a permutation block randomisation (1:1) by generating a set of random numbers where the even numbers define a block of specified ordered randomly treatments assignment and the odd numbers define other order of assignment of treatments. The random permuted blocks method should achieve balanced experimental groups.

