### Study intervention

Participants will be randomly assigned to either the intervention or treatment-as-usual groups.

Participants in the intervention group will have access to the usual treatment programmes at CRPS, but will also enrol into twice weekly 50 min sessions of strength-based physical exercise over 12 weeks. Patients in the treatment-as-usual group will continue accessing the traditional CRPS programmes, but will not participate in the strength-based exercise sessions.

The exercise sessions will be carried out at the ‘Contemporánea’ Physiotherapy Clinic in Salamanca (https://www.fisiocontemporanea.com/).

In accordance with previous studies involving moderate exercise training programmes for patients with schizophrenia, the duration of the intervention will be limited to 12 weeks.^26,27^ The training sessions will follow an evidence-based physical activity programme with successful outcomes on telomere length in healthy populations,^23^ and will be structured as follows:
Part 1: Warm-up with an aerobic component lasting approximately 15 min.Part 2: Twelve multi-analytical exercises based on the strength endurance component. Six of these exercises will be performed during the first weekly session, and the rest during the second. Each exercise will comprise three sets of 12 repetitions. The proposed exercises are as follows:
First session: squat and row with band; glute bridge and kettlebell chest press; backward lunge and abdominal pull-off with band; push up; glute kickback with band; abdominal crunch.Second session: wall ball squat; step up and kettlebell overhead press; abdominal pull-off and lateral split squat with slider; pullover with band; kettlebell deadlift; kettlebell split squat.Part 3: Cool-down phase with breathing and stretching exercises.Before the intervention begins, participants will undergo two to three preparation sessions, in which they will practice the exercises that they will later carry out over the 12 weeks.

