### Sample size

Because of the lack of previous interventional studies looking into changes in telomere length following physical exercise in patients with schizophrenia, the sample size calculation was based on a pre–post study, using the proposed intervention in elderly healthy participants.^23^ Accordingly, for an identified Cohen's effect size of 1.1, a statistical power of 90% and an alpha level of 0.05 with a one-sided contrast, we would need a sample size of 32 individuals (16 per group). To account for potential study losses, a 20% lost-to-follow-up rate was considered, leading to a required sample of 40 participants (20 per trial arm). We employed the R Statistical Software pwr package for this calculation (version 4.4.2 for Windows, The R Foundation; https://www.r-project.org/).

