### Limitations

Our study has some limitations mainly related to its pragmatic nature. For example, trial participants´ physical activities outside of the healthcare system will not be controlled, and there will not be a healthy volunteer group to make comparisons. Nonetheless, our study population tends to live a more passive life in terms of physical exercise than the general public; thus, it is unlikely that this would affect the trial findings. To further temper this limitation, all trial participants will be administered the International Physical Activity Questionnaire to monitor their pre-trial physical activity levels. Also, there is evidence suggesting that telomere length may vary depending on whether samples are obtained from saliva or peripheral blood.^42^ Nevertheless, we shall use saliva samples in all our measurements, which will avoid potential bias related to the DNA extraction methodology. Furthermore, telomere length may be affected by many factors, such as smoking tobacco, alcohol consumption and socioeconomic deprivation. We will take this information into consideration for the analysis and interpretation of the results; however, since the study does not entail any other change in the patients´ life than a possible allocation to a strength-based training exercise programme, if this eventually had an effect, it would still be reflected in intra-individual telomere length changes. The study will be carried out in only one site and will include a relatively low number of participants, which may affect the generalisability of the results and, therefore, it may need to be replicated elsewhere. Given the pragmatic nature of this trial, other factors that may affect telomere length, such as smoking tobacco, will not be controlled.

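### The even/odd randomisation rule allows only two block orders, so at least half of the allocations follow from earlier ones; block size is not stated

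*Protocol article*

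**What the plan says.** The Randomisation section of the protocol article announces the method: "We shall carry out a permutation block randomisation (1:1) by generating a set of random numbers". It then gives the generating rule: "the even numbers define a block of specified ordered randomly treatments assignment and the odd numbers define other order of assignment of treatments". The section expects this to yield balanced groups and calls it the random permuted blocks method. It gives no block size and does not mention varying sizes.

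Two other sections bear on how much this matters. Under Limitations: "The study will be carried out in only one site". Under Study intervention: "Patients in the treatment-as-usual group will continue accessing the traditional CRPS programmes, but will not participate in the strength-based exercise sessions". The arms therefore differ by something that staff and patients can see. The article section on sample size sets 40 randomised patients, 20 per arm.

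**The concern.** A random number is either even or odd, and the rule attaches one block order to each. Two orders are then possible per block, whatever its length. Two balanced sequences agree up to some position, differ there, and are both fully known afterwards. Someone who knows the two orders and has seen the earlier assignments in the block faces one uncertain allocation per block and no more.

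Randomisation protects the comparison only if the person enrolling a patient cannot foresee the arm. If the next arm can be foreseen, fitter or more motivated patients can be steered towards exercise. The eligibility judgement about ability to train at moderate intensity leaves some room for that. The Short Physical Performance Battery (SPPB) and the Brief Assessment of Cognition in Schizophrenia (BACS) depend on effort and fitness, so they are the outcomes most plausibly affected.

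**Working it through.** **The plan's own figures.** The article states no predictability figure. Its sample size can be checked: the inputs are "effect size of 1.1, a statistical power of 90% and an alpha level of 0.05 with a one-sided contrast". A two-sample t calculation gives 15 per arm (power 0.902), so the stated 16 per arm is adequate. With 20% loss, 32 / (1 − 0.20) = 40. The randomisation issue does not change these numbers.

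**Step 1: two orders per block.** Let b be the block size (assumed, since it is not stated). One position per block is uncertain, so:
- share determined = (b − 1)/b
- share guessed correctly = (b − 1 + 0.5)/b, because the one uncertain position is a coin toss.

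Size 2: 1/2 = 50% and 1.5/2 = 75%. Size 4: 3/4 = 75% and 3.5/4 = 87.5%. Of 40 patients, that is 20 and 30 determined. Enumerating every possible pair of balanced orders gives the same shares, so it does not matter which two are chosen. Larger blocks are worse: 83% are determined at size 6.

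**Step 2: all orders per block.**
- Size 4, six orders. The chance of being determined at positions 1 to 4 is 0, 0, 1/3, 1: (4/3)/4 = 33%. The chance of a correct best guess is 1/2, 2/3, 2/3, 1: 2.833/4 = 70.8%.
- Size 6, twenty orders. Determined: 0, 0, 0, 0.1, 0.4, 1: 1.5/6 = 25%. Best guess: 0.5, 0.6, 0.6, 0.7, 0.7, 1: 4.1/6 = 68.3%.

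Of 40 patients, that is 13.3 and 10 determined. At size 2 only two orders exist, so using all of them changes nothing.

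**Step 3: possible effect on the error rate.** Assumptions, none of them from the article: a recruiter acts on every guess; each guess shifts the patient's value on the compared quantity by τ = 0.1 to 0.2 SD towards the guessed arm; there is no true effect; the test is two-sided at 5% with 16 per arm. With guess accuracy p, each arm's mean moves by τ(2p − 1) in opposite directions, so bias = 2τ(2p − 1). The rejection rate comes from the noncentral t distribution with 30 degrees of freedom and noncentrality bias × √(16/2).

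| Scheme | p | Bias (SD), τ = 0.1 to 0.2 | Two-sided error |
|---|---|---|---|
| Two orders, size 2 | 0.750 | 0.10 to 0.20 | 5.9% to 8.5% |
| Two orders, size 4 | 0.875 | 0.15 to 0.30 | 7.0% to 13.0% |
| All orders, size 4 | 0.708 | 0.083 to 0.167 | 5.6% to 7.4% |
| All orders, size 6 | 0.683 | 0.073 to 0.147 | 5.5% to 6.9% |

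The fair comparator is the lower half of the table, not 5%, because a conventional list with a fixed, known block size is also partly predictable.

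**The case against.** The strongest reply is that at block size 2 the orders AB and BA are all there are, so the even/odd draw is complete permuted-block randomisation. A rule that names exactly two orders fits size 2 at least as naturally as size 4. This stands. A reader might infer that the method is not permuted-block randomisation at all; the article does not support that, since it depends on a block size it never gives. At size 2 the excess error over full blocks of 4 is only about 0.3 to 1.1 percentage points.

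Second, predictability does not by itself create bias. It also needs one-by-one enrolment and recruiters who know the orders and the earlier allocations. The article settles none of this. If a whole cohort were enrolled before randomisation, the risk would largely disappear. This also stands. Custody and concealment of the list may be described in the full protocol, and their absence from an article is not held against it here. Concealing the list would not fully cure a two-order scheme, however, if earlier assignments can be seen.

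Third, the primary outcome is a laboratory measurement, and the Data analysis section plans a group-by-time analysis in which stable baseline differences cancel. Steering would have to alter the 12-week change. Nothing in the article supports a shift of 0.1–0.2 SD in telomere change, so a reader who infers that the primary comparison is biased goes beyond the text.

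**Conclusion.** The point holds as a weakness in a method that the article states, not as a missing detail. On its plain reading the rule gives two block orders, and at least 50% of allocations are then determined by earlier ones. The figure is 50% at size 2 and 75% at size 4, both assumed sizes. At size 2 the fault is the small fixed block; above that, the rule drops valid permutations.

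The consequence is conditional. If enrolment is sequential, earlier allocations are known and guesses are acted on, the error rate under the assumed steering is about 6–8.5% (size 2) or 7–13% (size 4), against about 5.5–7.4% for full blocks of 4 or 6. Quoting 7–13% alone would present the worse of the two sizes as the expected result. Bias is most plausible for SPPB and BACS and less clear for change in telomere length. The sentence is also awkwardly worded, and the authors may have used a fuller scheme than it describes. This should be fixed; the text does not show that the trial's result is invalid.

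**What to change.** Replace the even/odd rule with a computer-generated 1:1 permuted-block list that draws from all balanced orders, with block sizes varying at random (for example 4 and 6) and not disclosed to recruiters. Even to someone who knew each block's size, the determined share would then lie between 25% and 33%; hiding the sizes lowers what can be foreseen in practice. The cost is minutes of programming and one rewritten paragraph, with no change to sample size or visits. The downside is a possible final imbalance of up to three patients if the last block is incomplete.

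The Method section dates the study from 1 January to 1 September 2024 and the article was published on 26 September 2024, so allocation may already be complete. In that case, report the block size and the orders actually used, say whether patients were randomised singly or as a cohort, and state the predictability as a limitation.

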### Data analysis

We shall describe data emerging from the study by using means and s.d., and medians and interquartile ranges for quantitative variables, and percentages for qualitative values. Normality will be assessed with the Kolmogorov–Smirnov test with the Lilliefors correction, and by examining box plots.

For group comparison, we shall employ the *t*-test for independent variables when these follow a normal distribution, and non-parametric Mann–Whitney *U-*test for non-normal distributions. The Levene test will be used to assess population equality variances. To analyse changes over time for unidimensional measurement tools within the trial groups, a two-factor analysis of variance will be used, with one factor being independent variables (intervention and treatment-as-usual group) and the other dependent (pre, post). If the tool has multiple dimensions, a three-factor analysis of variance will be used, with one independent factor (intervention, control) and two dependents (time: pre–post and dimension). In the event that there is missing data, we will use mixed models. We shall also use *post hoc* Bonferroni corrections.

All parameters will be presented with 95% confidence intervals, and statistical significance will be determined when *P*-values are <0.05. Data analyses will be performed with IBM SPSS version 28 for Windows and R statistical software.

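### A normality test on 16 to 20 participants per arm picks the between-group test, leaving test and estimand unfixed; name one baseline-adjusted analysis of telomere length instead

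*Protocol article*

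**What the plan says.** The Data analysis section sets a screen and a branch. The screen is: "Normality will be assessed with the Kolmogorov–Smirnov test with the Lilliefors correction, and by examining box plots". The branch is a t-test for "independent variables when these follow a normal distribution, and non-parametric Mann–Whitney" U otherwise. The section gives no significance level for the screen, no rule for when the formal test and the box plots disagree, no default test, and no effect measure common to both branches, although it promises 95% confidence intervals for all parameters.

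For change over time the same section plans other analyses: "a two-factor analysis of variance will be used, with one factor being independent variables (intervention and treatment-as-usual group") and time (pre, post) as the other factor, a three-factor version for tools with several dimensions, and, for incomplete data, "In the event that there is missing data, we will use mixed models". None of these depends on the normality screen, and none has a stated non-parametric alternative. The article does not say which analysis is primary for telomere length.

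The Sample size section gives 16 evaluable and 20 randomised participants per arm.

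**The concern.** The printed rule lets the outcome data select the test. Three things follow.

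- The screen has little information at this size. A pass is weak evidence of normality, and a fail can be chance. Reading box plots adds a judgement that cannot be reproduced.
- The branch changes the question. The t-test concerns a difference in means. Mann–Whitney concerns whether values in one arm tend to exceed those in the other, and gives no mean difference to report.
- The section is not consistent with itself. Telomere values could fail the screen for the group comparison and still go into a normal-theory analysis of variance or mixed model.

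At stake is whether the reported effect and its P-value come from a method chosen before the data were seen. In addition, the screened two-sample comparison as described makes no adjustment for the baseline value, which the trial collects.

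**Working it through.** **Inputs from the Sample size section.** Effect size 1.1, power 90%, alpha 0.05 one-sided, 16 per group evaluable, 20% loss, 20 per arm randomised.

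**The plan's own figure.** The exact one-sided two-sample t calculation at d = 1.1 needs 14.88, so 15 per arm; power at 16 per arm is 91.9%. The stated 16 per arm is reproduced to within one participant. Inflation: 32 / (1 − 0.20) = 40, as stated. The design therefore assumes a t-test on normal data.

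**Assumptions.** The documents give no SD or distribution for telomere length, so a range of shapes was used. The screen was taken as a Lilliefors test at 5% in each arm, with the t-test used only if both arms pass. Box plots were not modelled. Final tests were two-sided at 0.05. There were 20,000 simulated trials per scenario, with critical values from 200,000 normal samples.

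**Step 1: how often the screen switches the test.** Within an arm, D = max over i of {i/n − Φ(z(i)), Φ(z(i)) − (i − 1)/n}, where z(i) are the ordered standardised values. The 5% critical values are 0.213 (n = 16) and 0.192 (n = 20). If each arm fails with probability r, the trial goes to Mann–Whitney with probability 1 − (1 − r)².

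- Normal: r = 0.05, so 1 − 0.95² = 0.098 (simulated 0.099).
- Log-SD 0.5, n = 16: r = 0.275, so 1 − 0.725² = 0.474 (simulated 0.477).
- Log-SD 0.5, n = 20: r = 0.346, so 1 − 0.654² = 0.572 (simulated 0.572).

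| Assumed shape | To Mann–Whitney, n = 16 | n = 20 |
|---|---|---|
| Normal | 10% | 10% |
| t, 3 df | 39% | 46% |
| Lognormal, log-SD 0.5 | 48% | 57% |
| Exponential | 73% | 83% |
| Lognormal, log-SD 1 | 90% | 96% |

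**Step 2: error rates of the whole rule.** Overall type I error is 0.047 to 0.055 across all ten cells. At d = 1.1, power of the two-stage rule is within 2 percentage points of the better fixed test in every cell; the largest gap is at log-SD 0.5, n = 16: 0.907 against 0.923. Among trials that pass the screen, the t-test's type I error is 0.060 to 0.064 (log-SD 0.5), 0.074 to 0.077 (exponential) and 0.095 to 0.106 (log-SD 1). Passing the screen is therefore no guarantee for the test it releases, even though the overall rate is held.

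**Step 3: what a fixed test costs.** With normal data and d = 1.1, simulated power is 85% (t) against 83% (Mann–Whitney) at 16 per arm, and 93% against 92% at 20 per arm. Fixing the test costs essentially nothing.

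**Step 4: what baseline adjustment gains.** With pre–post correlation ρ, adjusting for baseline raises the standardised effect from d to about d / √(1 − ρ²). At assumed values d = 0.7 and ρ = 0.7: 0.7 / √(1 − 0.49) = 0.98. At 16 per arm with normal data, simulated two-sided power is about 75% for the adjusted model and 48% for the screened comparison of 12-week values. The gain depends on ρ: at 0.5 the adjusted model reaches about 59%, and at 0.3 about 50%. A comparison of change scores, which is what the group-by-time term tests, gives d / √(2 − 2ρ) = 0.7 / √0.6 = 0.90 at ρ = 0.7 and power of about 70%, so against that analysis the gain is small.

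**The case against.** The strongest reply has four parts.

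- **Scope.** The screen applies to group comparisons only. Change between arms has its own unscreened analysis, and with 20% loss foreseen the mixed models may well be used. The Limitations section looks for the effect in within-person change, which fits that analysis. The screened tests may serve only cross-sectional comparisons. This stands: a reader might infer that the primary P-value necessarily passes through the screen, but the article does not name the primary analysis, so that is not shown.
- **Error rates.** A reader might infer that the rule inflates alpha. Step 2 does not support this. Nor is disagreement between the two tests an error rate: they differ on significance in about 2 to 4% of simulated null trials and 3 to 12% at d = 1.1, and any two valid tests differ sometimes.
- **Skew.** The documents do not show telomere length to be skewed. It comes from a 2^−ΔΔCt calculation and is positive, which makes skew plausible, but a reference sample is used to obtain absolute lengths, and change scores may have another shape. The 48% is conditional on an assumption.
- **Details that should not be charged to the plan.** The article says that Levene's test will assess equality of variances; it states no switch triggered by it. Mann–Whitney can be run on change scores, and the plain t-test does not adjust for baseline either, so the fallback is no worse than the default on that count.

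What remains is that the rule is printed as a choice and is not a gap to be filled by an analysis plan. At this sample size it selects the test largely by chance over a plausible range of shapes, and it conflicts with the unscreened analyses beside it.

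**Conclusion.** The point holds in a limited form. The section lets a weak formal test and a subjective plot choose between two tests with different estimands, while parallel analyses of the same outcome proceed as if normality were settled. About 10% of trials would switch by chance with normal data. About 48% (16 per arm) or 57% (20 per arm) would switch under assumed lognormal skew with log-SD 0.5. The damage is an unfixed test and estimand, and avoidable loss of precision if the screened comparison of 12-week values carries the result (75% against 48% power at the assumed correlation of 0.7 and shift of 0.7 SD). Overall type I error is essentially unaffected.

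The figures rest on assumed distributions, a 5% screen in each arm, and no allowance for the box-plot judgement. How far the primary result is affected depends on which analysis is primary, which the article leaves open. The change is worth making before outcome data are seen.

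**What to change.** Delete the normality-test rule for between-group outcome comparisons. Name one primary analysis of telomere length: a linear model of the 12-week value on arm and baseline value (ANCOVA), or the equivalent mixed model if data are missing, reporting the adjusted difference with its 95% confidence interval.

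Fix the scale before outcome data are seen. The log scale is reasonable for a positive quantity derived from qPCR, with the result back-transformed to a ratio of geometric means. It need not carry over to bounded secondary scores such as the SPPB.

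Add one pre-named sensitivity analysis, for example a permutation test of the same adjusted contrast, and run it whatever the distribution looks like. Box plots and residual plots can stay as description, provided they do not select the test. Robust standard errors are optional.

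Cost: analysis wording and one extra sensitivity run. No additional participants or measurements are needed, because the baseline value is already collected.

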#### Secondary variables and outcomes

##### Cognitive function

Cognition will be assessed with the Brief Assessment of Cognition in Schizophrenia (BACS).^34^ The BACS score ranges from 0 to 100 points, with a higher score indicating better cognitive performance within the normative population.

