##### Frailty

Frailty will be measured with the Short Physical Performance Battery scale (SPPB),^35^ which comprises three components: a balance test, walking time and standing from a seated position. The maximum score is 12 points, with a higher score indicating better physical functioning.

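### The three-factor ANOVA for multi-dimension tools is not tied to the single overall scores that describe BACS, SPPB and EQ-5D-5L; each overall score should be the endpoint, analysed with baseline adjustment

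*Protocol article*

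**What the plan says.** The Data analysis section of the protocol article sets two rules for change over time. For single-dimension tools: "To analyse changes over time for unidimensional measurement tools within the trial groups, a two-factor analysis of variance will be used", with group and time as factors. The second rule begins "If the tool has multiple dimensions" and continues: "a three-factor analysis of variance will be used, with one independent factor (intervention, control) and two dependents (time: pre–post and dimension"). The section does not name the tools under each rule, the model term that answers the objective, or a common scale or direction for the dimensions. It also provides a generic comparison of groups ("For group comparison, we shall employ the *t*-test for independent variables when these follow a normal distribution", otherwise Mann–Whitney) and adds: "We shall also use *post hoc* Bonferroni corrections".

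The outcome sections describe each secondary outcome by one number. For cognition: "The BACS score ranges from 0 to 100 points". The SPPB has a maximum of 12 and the EQ-5D-5L runs from 0 to 100. In all three, higher is better. Components are named only for the SPPB, "which comprises three components: a balance test, walking time and standing from a seated position".

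**The concern.** Taken literally, the rule sends the SPPB to a model built on its components, although the Frailty section describes the outcome by its total. Whether BACS and EQ-5D-5L also go there cannot be told from the text.

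The group-by-time term of the three-factor model pools the dimensions with equal raw weight. That answers a clear question only if they are on one scale and point the same way. If they are not, the result is a mix whose weights are set by the spread of each dimension, and its effect size is hard to interpret. The analyst could also choose, after seeing the data, between total and dimensions, raw and scaled values, and the two interaction terms. Three of the five secondary objectives (cognition, frailty, quality of life) depend on this. Separately, the test uses the baseline only by subtraction, which is less efficient than adjusting for it.

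**Working it through.** **Inputs.** From the protocol: 16 evaluable patients per arm, two time points, and the outcome descriptions above. The protocol gives no SDs, correlations or subscale effects, so those below are assumptions. Power is two-sided at 0.05.

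**The plan's own figure.** With d = 1.1, one-sided alpha 0.05 and 90% power, the noncentral t gives 15 per group (power 0.902); 16 gives 0.919. Then 32 / (1 − 0.2) = 40. The stated size is reproduced within two patients and is not in question.

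**1. Outcomes against rules.**

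| Tool | Described as | Components named | Rule on a literal reading |
|---|---|---|---|
| BACS | one score, 0–100 | none | not determined |
| SPPB | total, maximum 12 | three | three-factor |
| EQ-5D-5L | one score, 0–100 | none | not determined |

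**2. What the group-by-time term tests.** With k dimensions, let D = (1/k) × Σ(post − pre) for each patient. The term's F is the square of the two-sample t on D. In one simulated data set (16 per arm, k = 3), F = 5.8406 and t² on the summed change = 5.8406. So if a total is the plain sum of its components as entered, this term is the test on the total.

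**3. Unequal spread.** If one dimension has r times the SD of the others and changes are independent, its share of the variance is r² / (r² + k − 1):
- k = 3: 9/11 = 82% for r = 3; 100/102 = 98% for r = 10.
- k = 6: 9/14 = 64% for r = 3; 100/105 = 95% for r = 10.

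**4. Power can move either way.** Assume six dimensions with SDs 15, 10, 5, 4, 3 and 2, between-dimension correlation 0.3 and pre-post correlation 0.6. The variance of the raw sum is 0.7 × 379 + 0.3 × 39² = 721.6 (SD 26.86). For the z-scored sum it is 6 + 30 × 0.3 = 15 (SD 3.873). The change-score effect is d / √(2 × (1 − 0.6)) = d / 0.894, and the noncentrality is that value × √(16/2).

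| 0.8 SD benefit on | d, raw | Power, raw | d, z-scored | Power, z-scored |
|---|---|---|---|---|
| four lowest-SD | 11.2/26.86 = 0.417 | 24.8% | 3.2/3.873 = 0.826 | 71.5% |
| all six | 31.2/26.86 = 1.161 | 94.4% | 4.8/3.873 = 1.239 | 96.6% |
| four highest-SD | 27.2/26.86 = 1.013 | 87.2% | 0.826 | 71.5% |
| two highest-SD | 20/26.86 = 0.745 | 62.5% | 1.6/3.873 = 0.413 | 24.4% |

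The ranking reverses with the location of the benefit. A plain total of the raw dimensions has the same power as the raw column, by step 2.

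**5. Gain from baseline adjustment.** With pre-post correlation ρ and equal variances, the variance is 2(1 − ρ) for change and 1 − ρ² for ANCOVA. The ratio is (1 + ρ)/2: 0.65 at ρ = 0.3, 0.80 at 0.6 and 0.90 at 0.8. For d = 0.826 and ρ = 0.6:
- Change: 0.826/0.894 = 0.924; noncentrality 0.924 × 2.828 = 2.61; power 71.5%.
- ANCOVA: 0.826/0.8 = 1.033; noncentrality 2.92 on 29 df. This gives 81% if chance baseline imbalance is ignored; simulation, which includes it, gives 79%.

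By the same formulas, power goes from 48% to 66% at ρ = 0.3, and from 95% to 96% at ρ = 0.8.

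**The case against.** The strongest reply is that the rule is conditional. A single overall score can go through the two-factor model or the t-test and Mann–Whitney comparison in the same section, and the dimension model can stand beside them. This stands in large part. A reader might infer that the plan contradicts its own outcome definitions; the text supports only that the two are not reconciled. The generic comparison does not close the gap, because it names no outcome and does not say whether it compares post values or changes.

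Second, where a total is the plain sum of equally scaled components, the criticised term is the test on the total. This is correct, and if the SPPB is entered that way there is no conflict. The section does not say that it is.

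Third, a reader might infer that the three-factor model generally loses power. Step 4 shows that it does not. A reader might also infer that raw times, where lower is better, cancel gains elsewhere. The Frailty section names walking time as a component but never says that raw times are analysed, and it states that a higher score is better. Nor is sphericity an issue for the group-by-time test, which has two time levels and one degree of freedom; it concerns only the dimension terms.

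Fourth, the three-way term and Bonferroni follow-up can examine single dimensions. They can, but the three-way term asks whether effects differ between dimensions, not whether patients improved, and the Bonferroni family is not defined.

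Last, an article may leave subscale scoring to a fuller document. That is fair for scoring details. The choice of model is stated here and can be judged as stated.

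**Conclusion.** The point holds in limited form. The protocol assigns multi-dimension tools to a model whose group-by-time term is an unadjusted change-score test on the raw mean of the dimensions, and it does not link that model to the overall scores that describe the secondary outcomes. On the protocol's wording this is shown for the SPPB only.

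The effect of pooling unlike dimensions has no fixed sign or size. It depends on SDs, correlations and the location of the benefit, none of which the protocol gives. What can be improved without new data is the match to the described outcomes and the efficiency of the test. The gain from about 71% to 79% rests on an assumed pre-post correlation of 0.6, equal variances and 16 per arm; it is larger at lower correlations and small at high ones. Only secondary outcomes are involved. It is worth changing, but it does not threaten the trial's main result.

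**What to change.** State that the overall score of each tool, as described in the outcome sections (BACS 0–100, SPPB up to 12, EQ-5D-5L 0–100), is that tool's single secondary endpoint. Analyse it by ANCOVA of the post value on group and baseline, in place of the repeated-measures interaction test, and report the adjusted difference with its 95% confidence interval. Drop the three-factor ANOVA. Where dimensions are reported, give them as supportive baseline-adjusted differences on a common scale (for example, baseline-SD units), oriented so that higher is better.

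The cost is analysis wording only: no new data, visits or patients. The joint group-by-time-by-dimension test is given up.
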